## Abstract

Previous clinical trials for drug-susceptible tuberculosis (DS-TB) have shown that first-line treatment with doses of rifampicin up to 40 mg/kg are safe and increase the early treatment response for young adults with pulmonary tuberculosis. This may lead to a shorter treatment duration for those persons with TB and a good baseline prognosis, or increased treatment success for vulnerable subgroups (age > 60, diabetes, malnutrition, HIV, hepatitis B or hepatitis C coinfection, TB meningitis, stable chronic liver diseases). Here, we describe the design of a phase 2b/c clinical study under the hypothesis that rifampicin at 35 mg/kg is as safe for these vulnerable groups as for the participants included in previous clinical trials. RIAlta is an interventional, open-label, multicenter, prospective clinical study with matched historical controls comparing the standard DS-TB treatment (isoniazid, pyrazinamide, and ethambutol) with rifampicin at 35 mg/kg (HR^35^ZE group) vs. rifampicin at 10 mg/kg (historical HR^10^ZE group). The primary outcome is the incidence of grade ≥ 3 Adverse Events or Severe Adverse Events. A total of 134 participants will be prospectively included, and compared with historical matched controls with at least a 1:1 proportion. This will provide a power of 80% to detect non-inferiority with a margin of 8%. This study will provide important information for subgroups of patients that are more vulnerable to TB bad outcomes and/or treatment toxicity. Despite limitations such as non-randomized design and the use of historical controls, the results of this trial may inform the design of future more inclusive clinical trials, and improve the management of tuberculosis in subgroups of patients for whom scientific evidence is still scarce. Trial registration: EudraCT 2020-003146-36, NCT04768231.

## 1. Introduction

Current standard treatment for drug susceptible tuberculosis (DS-TB) was designed 40 years ago and has remained unchanged except for a 4-month regimen using high-dose rifapentine and moxifloxacin following the results of a recent clinical trial [1]. Rifampicin is still the backbone drug in the treatment of DS-TB because of its potent bactericidal and sterilizing activity. The currently used once daily 10 mg/kg dosing of rifampicin was selected in the 1970s and was based on pharmacokinetics, toxicity, and cost concerns [2]. Under clinical trial conditions and using per protocol analysis, the current standard regimen achieves a 95% efficacy [3]. However, several pharmacological, bacterial, and host factors may negatively affect treatment outcomes in daily practice.

Some groups of people are more vulnerable to TB because of risk factors (e.g., advanced age, immunosuppression, diabetes, or liver disease) that increase their risk of active disease and poor treatment outcomes [4]. For example, treatment success rate was 86% globally, but only 77% for people living with HIV [5]. Drug-induced liver injury is the best-known adverse reaction associated with rifampicin, isoniazid, and pyrazinamide. In addition, rifampicin typically causes gastrointestinal symptoms and hypersensitivity reactions (pruritus, rash, flu-like syndrome, hemolytic anemia). Although for clinicians these groups are also considered more vulnerable to adverse reactions, different studies show contradictory results. For example, in a retrospective study including 1149 patients, age > 60, diabetes, and hepatitis B virus (HBV) infection were not associated with an increased risk of adverse reactions [6].

Optimal drug regimen, dose, and treatment duration are still not well established, as these vulnerable groups were underrepresented in previous clinical trials as these were conducted in mid-to-high TB burden countries. However, the population in these studies included young participants with pulmonary TB and no comorbidities except 20% of participants with HIV coinfection (data from a systematic review by the European South American TB Research Collaborative Network (EUSAT-RCS, manuscript in preparation). A rifampicin dose ranging trial in DS-TB patients by Boeree and colleagues reported that doses (up to 50 mg/kg) were safe and tolerated, and further improved the extended early bactericidal activity in TB patients [7,8]. The optimized doses achieved up to 10-fold higher exposure in plasma (AUC0-24) and a higher early bactericidal activity measured by a decline in the colony-forming units count in sputum culture [7,9,10]. A meta-analysis of 13 studies from 1979 to 2021, including adults with TB meningitis and pulmonary TB receiving doses up to 35 mg/kg, did not show an increase in the incidence of Severe Adverse Events (SAE), with a pooled Incidence Risk Ratio of 1.00 (95% confidence interval 0.82–1.23) [11]. Therefore, increased doses might have the potential to shorten DS-TB treatment. Pharmacokinetic studies show that a low proportion of patients reach target exposures with the current standard doses of rifampicin. For example, in a clinical trial in Indonesia, only 48% of the participants receiving standard dose rifampicin reached the 8 mg/L threshold for maximum plasma concentrations (Cmax) deemed to be effective [12]. In addition, adults with TB and other comorbidities such as HIV and diabetes may have lower exposure to rifampicin [13]. In the absence of actual AUCs, clinicians often use the concentration 2 h after drug intake as a predictor of rifampicin exposure [14].

The RIAlta study aims to evaluate the safety and efficacy of rifampicin at 35 mg/kg daily for the intensive phase of the first line TB treatment in vulnerable adults with TB, usually excluded from clinical trials due to age and/or comorbidities. This is a single arm prospective study using matched historical controls. This article summarizes the trial protocol and the rationale behind key aspects of its design.

## 2. Methods

### 2.1. Study Design

This is an interventional, open-label, multi-center, historically matched controlled prospective clinical study of high dose rifampicin (35 mg/kg, HR^35^ZE group) versus standard-dose (10 mg/kg/day, historical HR^10^ZE group) in a vulnerable population. Clinical trials with rifampicin are typically open label as the drug causes orange discoloration of the urine and other body fluids that makes it difficult to maintain blinding for participants and investigators [15,16,17]. Table 1 shows a comparative of key design aspects in different phase 2 studies using high-dose rifampicin in the last 15 years.

### 2.2. Objectives and Endpoints

The study primary objective is to evaluate the safety of high-dose rifampicin (35 mg/kg/d) as part of a standard first line regimen using standard doses of isoniazid (5 mg/kg), pyrazinamide (25 mg/kg), and ethambutol (15–25 mg/kg) for 8 weeks in adult subjects with pulmonary or extrapulmonary DS-TB belonging to difficult to treat subgroups. The secondary objectives are to evaluate the tolerability, efficacy, bactericidal activity, pharmacokinetic/pharmacodynamics, and cost effectiveness of high dose rifampicin, among others. 

The primary safety endpoint is the proportion of participants and historical controls with one or more grade 3 or higher adverse events (AE) according to the CTCAE v5 or SAE at 8-weeks after treatment with high-dose rifampicin onset. Table 2 below describes in detail the analysis population and primary safety outcomes. The secondary tolerability endpoint includes the proportion of participants with any AE. The secondary efficacy endpoint includes the proportion of participants and historical controls who have sputum culture conversion at 8 weeks after treatment onset or a proportion of participants with clinical improvement according to the treating physician (if follow-up images are available for extra-pulmonary TB) but without a follow up sample at 8 weeks after treatment onset.

Most TB phase 2 trials complete their intervention at week 8 or earlier and then participant care is transferred to a public institution within the National TB programs, so the information about end of treatment and post-treatment outcomes is scarce [10,17,18]. In the RIAlta trial, after the intervention and the primary safety objective evaluation, an extended follow-up period will be offered to participants, in line with the phase 2b/c design suggested by Phillips et al. [19]. This will provide information about end-of-treatment outcomes and relapse incidence in the prospective group.

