### 2.4. Study Population and Eligibility 

Adult participants ≥18 years with confirmed or probable pulmonary or extrapulmonary TB will be eligible to participate in the study. Additionally, trial candidates must be older than 60 years or have one of the following: diabetes, HIV, HBV or HCV coinfection, malnutrition (body mass index below 18.5 kg/m^2^), or any other chronic but stable liver disease. 

Adult participants with *M. tuberculosis* that is rifampicin-resistant by Xpert MTB/RIF or by drug susceptibility testing; with a Barthel index < 40 or life expectancy of less than 2 months regardless of anti-TB treatment; with signs of hepatotoxicity characterized by AST or ALT > 5x upper limit of normal, total bilirubin > 3x upper limit of normal, Child–Pugh grade C cirrhosis or acute decompensation at enrollment, or any grade 3–4 hepatobiliary alteration; who were previously treated with first-line anti-TB drugs or quinolones for at least 14 days or current treatment for more than 7 days; with solid organ or bone marrow transplantation; with active neoplasm requiring chemotherapy or immunotherapy treatment; or with previous severe pulmonary disease other than TB according to the investigator’s judgment will be excluded from the study. Participants with aischemic heart disease OR severe arrhythmia within 6 months OR subjects with atrial fibrillation and indication of oral anticoagulant therapy when transitioning to low-molecular weight heparin is not feasible will also be excluded from the study. Lastly, pregnant or breastfeeding women and participants not suitable to be included according to the investigator will not be enrolled for the study.

This is one the key differential aspects of RIAlta’s design. Previous trials have included people living with HIV, but few participants with diabetes, age over 60, or chronic liver disease were included [11,22].

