### 2.7. Rifampicin Dosing Strategies

Study participants will receive high dose rifampicin 35 mg/kg for 8 weeks (maximum once daily dose of 3150 mg) by combining fixed-dose combination (FDC) tablets with rifampicin loose capsules (Table 3). We have adapted the WHO guidelines weight band dosing scheme for a more accurate rifampicin dosing. The dose for each band was calculated for the medium weight in each band (45 mg × 35 mg = 1575 mg, rounding 1500 mg), and for those with >80 kg, the dose is calculated for 90 kg (90 mg × 35 mg = 3150 mg).

One limitation is the scarcity of the 600 mg presentation for rifampicin, which would reduce the pill burden for the participants in this trial. For instance, as optimized doses of rifampicin come closer to daily practice, public health decision makers should advocate to increase the availability of rifampicin in high dose presentations to reduce the number of pills taken by patients.

To achieve a similar drug exposure to oral rifampicin at 35 mg/kg/day, the dose for intravenous administration should be 26 mg/kg/day [13].

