3. Modified intention to treat population	Includes a subset of intention-to-treat population with exclusion of some subjects in a justified way (subjects having non-tuberculous mycobacteria, early withdrawal of consent, etc.).	Includes subset of intention-to-treat population with exclusion of some subjects in a justified way (participants having non-tuberculous mycobacteria, early withdrawal of consent, etc.).
4. Microbiological intention to treat population	Includes all the participants that received at least one dose of anti-TB drugs AND have culture confirmation of DS-TB.	Includes all the participants enrolled in the study AND have culture confirmation of DS-TB.
5. Microbiological per-protocol population	Includes those participants who complete assigned follow-up AND were at least 80% adherent to study treatment AND have culture confirmation of DS-TB.	Includes those participants who complete assigned follow-up AND were at least 80% adherent to study treatment AND have culture confirmation of DS-TB.

**Table 3 pharmaceutics-15-00009-t003:** Weight-band dosing of rifampicin.

High Dose Rifampicin (35 mg/kg)	Weight-Band Dosing					
	35–40 kg	41–50 kg	51–60 kg	61–70 kg	71–80 kg	≥80 kg
**Rifampicin tablets** (300 mg)	900 mg 3 tablets	900 mg 3 tablets	1500 mg 5 tablets	1500 mg 5 tablets	1800 mg 6 tablets	2400 mg 8 tablets
**Rifampicin tablets** (150 mg)	-	150 mg 1 tablet	-	150 mg 1 tablet	150 mg 1 tablet	-
**Fixed dose combination** (*150 mg rifampicin, 75 mg isoniazid, 400 mg pyrazinamide, and 275 mg ethambutol*)	450 mg 3 tablets	450 mg 3 tablets	450 mg 3 tablets	600 mg 4 tablets	750 mg 5 tablets	750 mg 5 tablets
**Total rifampicin dose**	1350 mg	1500 mg	1950 mg	2250 mg	2700 mg	3150 mg

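### Table 3 gives an 80 kg participant two rifampicin doses, 2700 mg and 3150 mg; as a minor companion point, its tablets take ethambutol slightly below 15 mg/kg at 56–60 kg and from 92 kg

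*Protocol article*

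**What the plan says.** Section 2.2 of the protocol article sets the companion drugs inside the primary objective: "standard doses of isoniazid (5 mg/kg), pyrazinamide (25 mg/kg), and ethambutol (15–25 mg/kg) for 8 weeks". Ethambutol is the only one of the three given as a range.

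Section 2.7 says the daily rifampicin dose is made up "by combining fixed-dose combination (FDC) tablets with rifampicin loose capsules (Table 3". Each band's dose is worked out at a central weight. The example for 41–50 kg is "45 mg × 35 mg = 1575 mg, rounding 1500 mg" (the 45 is evidently kilograms). For the top band, "for those with >80 kg, the dose is calculated for 90 kg".

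Table 3 gives the content of one fixed-dose tablet as "150 mg rifampicin, 75 mg isoniazid, 400 mg pyrazinamide, and 275 mg ethambutol". It allots 3 such tablets in the 35–40, 41–50 and 51–60 kg columns, 4 at 61–70 kg, and 5 in each of the last two columns. Those last two columns are headed 71–80 kg (total rifampicin 2700 mg) and ≥80 kg (3150 mg).

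**The concern.** Two printed statements disagree about the same participant. Table 3 places 80 kg in two adjacent columns with different rifampicin totals, while Section 2.7 starts the top band above 80 kg. Staff dose from the table, and the table alone does not settle which column applies. Rifampicin is the study drug. The higher of the two doses lies just under the 40 mg/kg/day that Section 2.6 cites as the highest tolerated in younger people free of important comorbidity. This trial enrols a different population, including people with "any other chronic but stable liver disease".

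The companion point is milder. The ethambutol range in Section 2.2 is wide enough to absorb ordinary weight banding, and four of the six bands stay inside it throughout. Two do not, so the regimen described in the primary objective and the regimen Table 3 delivers differ slightly for some participants.

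**Working it through.** **Inputs.** Fixed-dose tablet: rifampicin 150 mg, ethambutol 275 mg (Table 3). Tablet counts and loose rifampicin by band: Table 3. Ethambutol range 15–25 mg/kg: Section 2.2. Design weights 45 kg and 90 kg are stated in Section 2.7; 55, 65 and 75 kg are inferred by the same rule. Weights are read in whole kilograms, as the band labels are.

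**Step 1: reproduce the table's rifampicin totals.** Total = loose 300 mg strength + loose 150 mg strength + 150 × fixed-dose tablets.

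| Band (kg) | Sum (mg) | Total in Table 3 (mg) |
|---|---|---|
| 35–40 | 900 + 0 + 450 = 1350 | 1350 |
| 41–50 | 900 + 150 + 450 = 1500 | 1500 |
| 51–60 | 1500 + 0 + 450 = 1950 | 1950 |
| 61–70 | 1500 + 150 + 600 = 2250 | 2250 |
| 71–80 | 1800 + 150 + 750 = 2700 | 2700 |
| ≥80 | 2400 + 0 + 750 = 3150 | 3150 |

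All six agree, so the table has been read correctly.

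**Step 2: the dose at 80 kg.**

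- Column 71–80 kg: 2700 / 80 = 33.75 mg/kg.
- Column ≥80 kg: 3150 / 80 = 39.4 mg/kg.
- Difference: 3150 − 2700 = 450 mg.
- Target: 35 × 80 = 2800 mg. The lower dose is 100 mg under it (3.6%); the higher is 350 mg over it (12.5%).
- Both columns carry 5 fixed-dose tablets, so only the loose rifampicin differs (1950 mg against 2400 mg).

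**Step 3: ethambutol delivered by the tablets in Table 3.** Dose per kg = 275 × tablets / weight. The 15 mg/kg floor is crossed at 275 × tablets / 15.

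| Band (kg) | Ethambutol (mg) | mg/kg across the band | mg/kg at design weight |
|---|---|---|---|
| 35–40 | 825 | 23.6–20.6 | – |
| 41–50 | 825 | 20.1–16.5 | 18.3 (45 kg) |
| 51–60 | 825 | 16.2–13.75 | 15.0 (55 kg) |
| 61–70 | 1100 | 18.0–15.7 | 16.9 (65 kg) |
| 71–80 | 1375 | 19.4–17.2 | 18.3 (75 kg) |
| above 80 | 1375 | 17.0 at 81 kg, falling | 15.3 (90 kg) |

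- Three tablets: 825 / 15 = 55.0 kg. At 56 kg, 825 / 56 = 14.73; at 60 kg, 825 / 60 = 13.75. The shortfall is 0.27 / 15 = 2% to 1.25 / 15 = 8%.
- Five tablets: 1375 / 15 = 91.7 kg. At 92 kg, 14.95; at 100 kg, 13.75; at 110 kg, 12.5. The top band has no upper weight limit, so the shortfall grows with weight.

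**The case against.** **On the 80 kg overlap.** It can be called a copy-edit: Section 2.7 already supplies the answer, and both doses stay under 40 mg/kg. That sets the size of the point and does not remove it. The table is the operative dosing instruction, and as printed it contradicts the text.

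**On ethambutol, much of the opposing case stands.**

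- Dosing at a central weight is disclosed, and drift at band edges follows from it. Rifampicin itself drifts further: 1500 mg at 50 kg is 30.0 mg/kg, 14% under 35.
- "This article summarizes the trial protocol", so the full document may provide separate ethambutol. The article is not a complete account of supply in any case. It also gives an intravenous rifampicin dose without saying how the companion drugs would then be given. The ethambutol point is therefore conditional.

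**Stronger readings that the documents do not support.**

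- *Isoniazid and pyrazinamide are underdosed as well.* The same tablets give 3.75 and 20.0 mg/kg at 60 kg. Section 2.2 states single values for these drugs, which fixed tablets cannot hit at every weight. A departure from a nominal value is not a breach of a stated range.
- *The 51–60 kg band should be split, with four tablets from 56 kg.* That brings ethambutol to 19.6–18.3 mg/kg but raises pyrazinamide to 28.6–26.7 mg/kg (1600 / 56 and 1600 / 60), above the stated 25. The Introduction says "Drug-induced liver injury is the best-known adverse reaction associated with rifampicin, isoniazid, and pyrazinamide", and the trial admits people with stable chronic liver disease. That is a clinical trade-off, not a correction.

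**Conclusion.** The 80 kg overlap is an error as written: one weight, two rifampicin doses 450 mg apart (33.75 or 39.4 mg/kg), with Section 2.7 supporting only the lower. A reader might infer that the upper column breaches the tolerated dose cited in Section 2.6. It does not, since 39.4 is below 40, though the margin is narrow and that figure comes from a healthier population.

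The ethambutol point is minor and conditional. If the fixed-dose tablets are the only source, ethambutol is 14.7–13.75 mg/kg at 56–60 kg and under 15 mg/kg from 92 kg, outside the range in Section 2.2. A reader might infer that the weight-band scheme as a whole underdoses ethambutol. It does not: no band is below 15 mg/kg at its design weight (55 kg gives exactly 15.0), and no band exceeds 25.

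Neither point touches the sample size, the non-inferiority margin or the analysis.

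**What to change.** 1. In Table 3, change the last column label from ≥80 kg to >80 kg, matching Section 2.7. A participant at 80 kg then has one dose, 2700 mg. Check that the full protocol and any dosing instructions held at the sites carry the same label.

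2. In Section 2.2, add one sentence, for example: *Companion drugs are given as fixed-dose tablets by weight band (Table 3); the per-kilogram doses are nominal, and ethambutol is slightly below 15 mg/kg at 56–60 kg and from 92 kg.* If the full protocol supplies ethambutol separately, say that instead.

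The cost is one symbol and one sentence. No tablet count changes, the rifampicin totals stand, and nothing in the sample size or analysis needs revisiting.

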### 2.3. Study Setting

The European South American TB Research Collaborative Network (EUSAT-RCS) is a consortium supported by the European Commission (Marie Sklodowska-Curie grant number 823890). The study will be carried out at four different TB treatment centers across Europe and one in South America. Vall d’Hebron Institute of Research (VHIR, Barcelona, Spain) is the sponsor of the study, and Hospital Universitario Vall d’Hebron (Barcelona, Spain) is the coordinating center and serves as the primary contact point for this trial. Other participating centers include: Radboud University Medical Center, Nijmegen, the Netherlands; University Medical Center Groningen, Groningen, the Netherlands; Centro Hospitalario Universitário de São João, Porto, Portugal; and Instituto Nacional de Enfermedades Respiratorias y del Ambiente (INERAM), Asuncion, Paraguay.

According to WHO 2020 data, TB incidence per 100,000 population is low in The Netherlands, Spain, and Portugal, whereas it is still high in Paraguay [5]. Diabetes prevalence is estimated to be 15% among people with TB, in contrast with 9.3% globally in 2019 [20]. Median age is between 42 and 46 years in Europe, whereas in high burden countries, the population is some 20 years younger on average (26 years in Paraguay, 27 in South Africa). Both South America and the European region have relatively low incidence rates of HIV-TB coinfection (3 in 100,000) [5]. In a UK prospective study, 18.1% of the patients with active TB had markers for hepatitis B or C infection were significantly higher than the 0.3% prevalence for the general population in the same period [21]. However, despite the need to study the possible increase in incidence, the potential drug interactions, and the risk of drug-induced liver injury with TB treatment, these coinfections are exclusion criteria for many TB trials (Table 1).

### 2.4. Study Population and Eligibility 

Adult participants ≥18 years with confirmed or probable pulmonary or extrapulmonary TB will be eligible to participate in the study. Additionally, trial candidates must be older than 60 years or have one of the following: diabetes, HIV, HBV or HCV coinfection, malnutrition (body mass index below 18.5 kg/m^2^), or any other chronic but stable liver disease. 

Adult participants with *M. tuberculosis* that is rifampicin-resistant by Xpert MTB/RIF or by drug susceptibility testing; with a Barthel index < 40 or life expectancy of less than 2 months regardless of anti-TB treatment; with signs of hepatotoxicity characterized by AST or ALT > 5x upper limit of normal, total bilirubin > 3x upper limit of normal, Child–Pugh grade C cirrhosis or acute decompensation at enrollment, or any grade 3–4 hepatobiliary alteration; who were previously treated with first-line anti-TB drugs or quinolones for at least 14 days or current treatment for more than 7 days; with solid organ or bone marrow transplantation; with active neoplasm requiring chemotherapy or immunotherapy treatment; or with previous severe pulmonary disease other than TB according to the investigator’s judgment will be excluded from the study. Participants with aischemic heart disease OR severe arrhythmia within 6 months OR subjects with atrial fibrillation and indication of oral anticoagulant therapy when transitioning to low-molecular weight heparin is not feasible will also be excluded from the study. Lastly, pregnant or breastfeeding women and participants not suitable to be included according to the investigator will not be enrolled for the study.

This is one the key differential aspects of RIAlta’s design. Previous trials have included people living with HIV, but few participants with diabetes, age over 60, or chronic liver disease were included [11,22].

